### Primary endpoint

The primary endpoint of this study is the rate of LNM. The scope of potential expanded indications for ESD is explored and evaluated based on the presence of LNM by histopathology and the positive rate of LNM with expanded indications for ESD.

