## Background

The improvement in public health awareness and the development of endoscopic technology have led to an increased detection rate and the overall incidence of early gastric cancer (EGC) [1, 2]. Statistics from the Chinese Association of Gastrointestinal Cancer Surgery show that EGC accounts for 19.5% of the overall gastric cancer cases in China [3]. Hence, scholars have begun to pay more attention to the early diagnosis and treatment of gastric cancer.

The current treatment methods for EGC mainly include endoscopic mucosal resection (EMR) or endoscopic submucosal dissection (ESD), and radical gastrectomy [4, 5]. However, the rate of lymph node metastasis (LNM) in early gastric cancer is low and, therefore, most patients undergo unnecessary or excessive lymph node dissection, which increases the surgical trauma [4]. Although EMR/ESD can be performed to completely remove the lesion, assessing the status of LNM around the stomach is currently impossible, resulting in incomplete treatment [6].

The absolute indications for ESD published in the updated Japanese gastric cancer treatment guidelines 2018 (5th edition) include the following: 1) differentiated intramucosal carcinoma with no ulcer and tumor size < 2 cm; 2) differentiated intramucosal carcinoma with no ulcer and tumor size > 2 cm; and 3) ulcerative, differentiated intramucosal carcinoma with tumor size < 3 cm that is accompanied by undifferentiated components [4]. However, controversy remains regarding the appropriate treatment for patients who exceed these absolute indications for ESD (i.e., expanded indications) [7–10]. Some studies found that ESD was suitable for some patients with EGC and expanded indications; these patients had better safety and effectiveness outcomes in the short-term after ESD [11]. Although the relative recurrence rate was increased in these patients, their long-term prognosis was better. Other studies recommend radical gastrectomy for patients with expanded indications because ESD may not meet the criteria for curative resection, and LNM may occur in the long-term [12, 13]. LNM is an independent risk factor for poor prognosis [14, 15]. Thus, a clinical trial, including patients with expanded indications for ESD, is necessary to select the treatment option that optimally balances radical tumor treatment and surgical trauma reduction.

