### Inclusion criteria

Patients aged 18–75 years (regardless of sex).Patients with Eastern Cooperative Oncology Group (ECOG) score ≤ 2 points and American Society of Anesthesiologists (ASA) score ≤ 2 points who can undergo a radical D2 gastrectomy.Patients without a history of gastrointestinal operation, chemotherapy, or radiotherapy.Patients with normal liver, kidney, heart, lung, and bone marrow function (GPT × 10^9^/L, PLT>10^9^/L).Patients who can understand and comply with the research protocol.Patients who can provide written informed consent by themselves or through their legal agent.Gastroscopic and pathologic diagnoses based on the following criteria: ①Tumor diameter > 30 mm, ulceration (UL)(+), and differentiated, mucosal carcinoma (T1a); ②Tumor diameter > 30 mm and differentiated, submucosal invasion depth < 500 μm (T1b SM1); ③Tumor diameter ≤ 30 mm and differentiated, submucosal carcinoma (T1b); ④Tumor diameter ≤ 20 mm, UL(−), and undifferentiated (T1a); ⑤Tumor diameter > 20 mm, UL(−), and undifferentiated (T1a); ⑥Tumor diameter ≤ 30 mm, UL(+), and undifferentiated (T1a); ⑦Tumor diameter > 30 mm, UL(+), and undifferentiated (T1a). The detailed inclusion criteria are shown in Table 1.

**Table 1 Tab1:** Inclusion criteria of expanded indications for ESD in patients with EGC

	T1a				T1b			
	UL (−)		UL (+)		SM1		SM2	
	≤20 mm	> 20 mm	≤30 mm	> 30 mm	≤30 mm	> 30 mm	≤30 mm	> 30 mm
**Differentiated**	ESD	ESD	ESD	EXPANDED	EXPANDED	EXPANDED	EXPANDED	SURGERY
**Undifferentiated**	EXPANDED	EXPANDED	EXPANDED	EXPANDED	SURGERY	SURGERY	SURGERY	SURGERY

ESD, ESD absolute indication; EXPANDED, ESD expanded indication; SURGERY, surgical indication for EGC; EGC, early gastric cancer; ESD, endoscopic submucosal dissection

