### Exclusion criteria

Patients with a contraindication for gastroscopy.Patients with uncontrollable diseases, such as coagulation disorders, epilepsy, central nervous system diseases or mental disorders, cardiopulmonary insufficiency, unstable angina, myocardial infarction, a cerebrovascular accident that occurred within 6 months, and other surgical contraindications.Patients who cannot undergo general anesthesia or surgical treatment because of conditions related to other organs, or patients who are unwilling to undergo surgery.Patients with gastric stump cancer, recurrent gastric cancer, multiple primary malignant tumors in the abdominopelvic cavity, or a history of other malignant tumors within the previous 5 years.Patients who are pregnant or lactating.Patients who are participating in other clinical trials.

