### Elimination criteria

A tumor with distant metastasis that is observed during the operation and postoperatively confirmed as advanced gastric cancer (pT_2_N_0_-_3_ M_0–1_) or non-gastric cancer by pathologic examination.Patients who do not follow the research plan and receive other anti-tumor treatments during the observation period.Patients with incomplete clinical data obtained after enrollment, which cannot be used in future statistical analysis.Patients who do not comply with the research protocol for treatment.Study termination as deemed necessary by researchers for the benefit of the patient.

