### Secondary endpoints

Accuracy, specificity, and sensitivity are evaluated using the following gold standards: postoperative histopathology of ultrasonic gastroscopy for tumor invasion depth, abdominal and pelvic enhanced computed tomography (CT) scan for LNM, pathological biopsy for tumor differentiation, and auxiliary examination for TNM staging.Cut-off values for LNM: A receiver operating characteristic curve is drawn for the clinical characteristics under different LNM rates to obtain the cut-off values.Logistic regression model: To explore the corresponding logistic regression model, postoperative histopathological examination for LNM, depth of infiltration, and degree of differentiation are evaluated in the univariate analysis. Variables with statistical significance in the univariate analysis are examined in the multivariate analysis.Complications: The incidence of postoperative complications within the last 30 days, including anastomotic fistula, pancreatic fistula, intestinal obstruction, delayed bleeding, and incision-related complications, are recorded. Postoperative complications classified as higher than Grade II, according to the Clavien–Dindo classification are regarded as clinically significant (Tables 2), [16].Five-year relapse-free survival rate: The time interval from the date of operation to the detection of tumor recurrence within 5 years is recorded.

**Table 2 Tab2:** Clavien–Dindo classification

Grade	Definition
I	Any complication that deviates from the natural course of the operation; treatments include antiemetic, antipyretic, analgesic, and diuretic drugs; infusion; physical therapy; as well as bedside debridement of incision infection.
II	Medications other than those permitted for grade I complications are required, including blood transfusion and total parenteral nutrition support.
III	Surgical and endoscopic interventions and radiotherapy are required.
IIIa	No general anesthesia is required.
IIIb	General anesthesia is needed.
IV	Life-threatening complications requiring intensive care.
IVa	Single-organ dysfunction
IVb	Multi-organ dysfunction
V	Death

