### Interventions

#### D2 gastrectomy

Under the requirement of the guideline for laparoscopic gastrectomy for gastric cancer (2016 edition) [19], laparoscopic radical gastrectomy is performed in patients. A preoperative abdominal enhanced CT scan is performed to evaluate the lesion site, tumor size, and LNM. Preoperative endoscopic injection positioning is performed with dye, or intraoperative endoscopic positioning is used to determine the tumor location to ensure safe margins. The scope of lymph node dissection (LND) is according to the Japanese gastric cancer treatment guidelines 2018 (5th edition) [4]. The scope of LND of D2 distal gastrectomy should include the No. 1, 3, 4sb, 4d, 5, 6, 7, 8a, 9, 11p, and 12a lymph nodes. D2 proximal gastrectomy should include the 1, 2, 3a, 4sa, 4sb, 7, 8a, 9, 11p, and 12a lymph nodes, and D2 total gastrectomy should include the 1, 2, 3, 4sa, 4sb, 4d, 5, 6, 7, 8a, 9, 11p, 11d, and 12a lymph nodes.

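### The lymph node metastasis rate used to judge expanded ESD indications includes any patient whose nodal disease was already evident on preoperative imaging; the rate among imaging node-negative patients should be prespecified beside it

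*Protocol article*

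**What the plan says.** **Endpoint.** The Primary endpoint section reads "The primary endpoint of this study is the rate of LNM" and continues "The scope of potential expanded indications for ESD is explored and evaluated based on the presence of LNM by histopathology". It neither restricts nor splits the rate by preoperative nodal findings.

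**Eligibility.** The tumour criteria open with "Gastroscopic and pathologic diagnoses based on the following criteria" and list seven categories. These, like Table 1, are defined by size, ulceration, differentiation and depth. The exclusion criterion closest to the topic is "Patients with gastric stump cancer, recurrent gastric cancer, multiple primary malignant tumors in the abdominopelvic cavity", which says nothing about regional nodes. The closest elimination criterion is "A tumor with distant metastasis that is observed during the operation and postoperatively confirmed as advanced gastric cancer"; N0-3 appears there only as part of the pT2 label.

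**Nodal imaging.** The D2 gastrectomy section states "A preoperative abdominal enhanced CT scan is performed to evaluate the lesion site, tumor size, and LNM". Data collection has all enrolled patients undergo an enhanced abdominal CT, PET/CT when necessary, and either ultrasound or magnified gastroscopy. Where ultrasound gastroscopy is done, its report should describe nodal metastasis around the stomach (Quality control of gastroscopy). Secondary endpoints include the accuracy of "abdominal and pelvic enhanced computed tomography (CT) scan for LNM" against postoperative pathology.

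**Rationale.** The Background says that with EMR or ESD, "assessing the status of LNM around the stomach is currently impossible, resulting in incomplete treatment".

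**The concern.** ESD removes the lesion and leaves the nodes. The Background gives this as its weakness. The nodal risk that bears on extending ESD is therefore the chance that metastasis is present when the preoperative work-up has not shown it. A patient with a small undifferentiated T1a tumour and metastatic nodes plainly visible on CT is eligible as the criteria stand, has a D2 gastrectomy, and counts as an event against that category. Overt and occult metastases are pooled.

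If there are such patients, the rate overstates the nodal risk of the patients for whom ESD would be in question. Few events are expected, and fewer still per category, so a small number of overt cases could colour the conclusion about a category.

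**Working it through.** **1. The plan's own figure.** Determination of sample size gives an expected rate p = 3%, an allowable error d = 1.5 points and one-sided α = 0.025 (z = 1.96).

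n = z² p(1 − p) / d² = 1.96² × 0.03 × 0.97 / 0.015² ≈ 496.8, rounded up to 497. The stated 497 is reproduced, so 1.5 points is the half-width of a 95% interval at 497 patients.

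**2. Can an overt node-positive T1 patient enter and stay in?** Inclusion: yes, since no nodal item appears. Exclusion: not triggered. Elimination: not triggered by regional nodes in a T1 tumour. The secondary endpoint points the same way, because the sensitivity of CT can be estimated only if CT-positive, pathology-positive patients may be enrolled.

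**3. Direction.** Let f be the share of all patients called node-positive on imaging and s the share of pathologically node-positive patients so called. Then:

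- rate in imaging-negative patients = p(1 − s) / (1 − f)
- shift = p − p(1 − s) / (1 − f) = p(s − f) / (1 − f)

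The shift is positive whenever s > f, that is, whenever imaging flags node-positive patients more often than patients in general.

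**4. Size, under assumptions.** The document gives neither f nor s. Assume f = 5% and s = 20% to 50%, and take the planned 3% as the all-patient rate.

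- Events: 497 × 0.03 = 14.9, about 15.
- Imaging-positive patients: 497 × 0.05, about 25, leaving 472.
- s = 20%: 3 events are overt; 12/472 = 2.5%, a shift of about 0.5 points.
- s = 50%: 7 events are overt (7.5 rounded down); 8/472 = 1.7%, a shift of about 1.3 points. Without rounding, 3 × 0.45 / 0.95 = 1.4 points.

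With f from 2% to 10% and the same s, the formula gives 0.3 points (3 × 0.10 / 0.90) to 1.5 points (3 × 0.48 / 0.98 = 1.47). With p = 3% and s no higher than 50%, the shift always stays below 1.5 points.

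**5. The other anchor.** Suppose instead that 3% is the imaging-negative rate, and that a share v of imaging-positive patients is node-positive on pathology. The all-patient rate is (1 − f) × 3% + f × v. At f = 5%, it is 2.85% + 0.5% = 3.35% for v = 10%, 2.85% + 1.5% = 4.35% for v = 30%, and 2.85% + 2.5% = 5.35% for v = 50%. The shift is then 0.35 to 2.35 points, so its size depends on the anchor as well as on the assumed inputs.

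**6. By category.** If 497 patients split evenly over the seven listed categories (assumption), each has about 71 patients and 71 × 0.03 = 2.1 expected events. One overt event moves a category's rate by 1/71 = 1.4 points.

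**7. Precision cost.** Half-width = 1.96 × √(0.03 × 0.97 / n): 1.50 points at 497, 1.51 at 487 (f = 2%), 1.54 at 472 (f = 5%) and 1.58 at 447 (f = 10%).

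**The case against.** The all-patient pathological rate is a coherent quantity. Table 1 defines the expanded indications by tumour features alone, and the endpoint matches that definition. No passage is contradicted. That the target is metastasis missed by the work-up is inferred from the Background, which does not say so. This stands, and it is why the all-patient rate need not be replaced as the sized primary endpoint.

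A reader might infer that the bias exceeds the planned precision. The document does not support this. f, s and v are all assumed. If 3% is read as the all-patient rate, the shift stays within the 1.5-point error. It exceeds 1.5 points only in some scenarios that read 3% as the imaging-negative rate, and the sample-size section does not say which reading applies.

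A reader might also infer that overt node-positive patients are being enrolled, or that a category will be wrongly rejected. The criteria allow the first but do not show it. For the second, no rate is given at which a category fails, and the scope is only to be explored and evaluated, with ROC cut-offs and a logistic model alongside. An upward bias would also err against widening ESD.

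Finally, restricting by CT alone is imperfect. Ultrasound gastroscopy and PET/CT can also show nodes, the CT report items name only non-local metastasis, and 280 of the 554 patients are retrospective, from 2008 onwards. This stands and shapes the fix.

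It could be said that a split by CT status is detail for an analysis plan. The tabulation is. Which rate supports the conclusion on indications is part of the endpoint's definition, and the Primary endpoint section settles that without the distinction.

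**Conclusion.** The point holds in a limited form. The criteria place no restriction on preoperative nodal status, and the expanded indications are judged on a rate over all patients. Any overt nodal metastasis therefore raises that rate relative to the patients for whom ESD would be in question. The direction follows if imaging carries any information on nodal status. The size cannot be known from the document: 0.5 to 1.3 points is an illustration that rests on 5% imaging-positive patients, 20% to 50% detection and 3% as the all-patient rate.

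This is not a contradiction in the protocol, and it does not show that the primary endpoint is wrong or that node-positive patients should be kept out. Excluding them would damage the CT accuracy endpoint. It is an avoidable mismatch between the rate reported and the use made of it, and data already planned can largely remove it.

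**What to change.** Keep all patients enrolled and keep the all-patient rate as the sized primary endpoint. In Primary endpoint, add:

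- the rate of pathological nodal metastasis among patients node-negative on preoperative imaging (CT in all, plus nodal findings from ultrasound gastroscopy or PET/CT where done), overall and by Table 1 category, with confidence intervals;
- a statement that the conclusion on expanded indications rests on this rate, with the all-patient rate beside it;
- the definition of node-positive on imaging, fixed before analysis.

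Under Quality control of radiographic examination, add regional nodal status to the CT report items. For retrospective patients, take it from the existing CT reports and count those with unknown status separately.

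The cost is endpoint wording, one template item, retrieval of old CT reports and a subset tabulation. The denominator shrinks slightly (half-width about 1.54 instead of 1.50 points if 5% are imaging-positive), and some nodal readings will be missing in the retrospective part.

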### Study design and setting

This is a multicenter, ambispective, observational, open-cohort study. The clinical trial was launched in May 2018 and will end in March 2022, with enrollment to be completed by December 2021. Between May 2018 and December 2022, patients from Beijing Friendship Hospital, Capital Medical University, Beijing Cancer Hospital, Peking University People’s Hospital, Peking University First Hospital, Chinese PLA General Hospital, and Cancer Hospital Chinese Academy of Medical Sciences will be selected for treatment. In total, 554 patients are expected to be included in the trial. After providing written informed consent, patients will undergo a D2 gastrectomy in a non-randomized, prospective study. For the retrospective study, researchers will recruit patients from January 2008 to April 2018, and all enrolled patients must meet the inclusion criteria. The detailed research process is described in Fig. 1. The latest protocol version is version 1.0 in April 2018.

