#### Data collection

A uniform case report form (CRF) was designed, and the electronic data capture (EDC) system was already established before the commencement of the clinical trial. All data are provided on the CRF. Subsequently, the clinical research coordinator (CRC) enters the data into the EDC system promptly (https://edc-cloud.medsci.cn/#/login). Every month, clinical research associates monitor the electronic database to ensure data quality.

The CRF includes the following data: 1) Demographic information: sex, age, length of hospital stay, body mass index, family disease history, concomitant disease, ECOG score, nutrition risk screening 2002 (NRS 2002) score, and venous thromboembolism score; 2) Perioperative laboratory tests: results of routine blood tests, biochemical investigations, and tumor marker evaluations, including CA19–9, CA125, AFP, CEA, and CA724; 3) Auxiliary examination: all the enrolled patients undergo an abdominal enhanced CT scan and low-dose plain CT scan of the chest, a positron emission tomography (PET)/CT examination when necessary, and an ultrasound gastroscopy or magnified gastroscopy; 4) Surgical information: ASA score, operation date, operation time, blood loss, surgical methods, degree of lymph node dissection, and intraoperative complications; 5) Postoperative pathology: the number of tumor lesions, tumor size, tumor location, surgical margin, gross type of tumor, histopathological type, Lauren type, depth of tumor invasion, number of lymph nodes dissected, and total number of LNM; and 6) Postoperative recovery outcomes: total hospitalization cost, postoperative complications and death, and recovery time of intestinal function (Table 3).

**Table 3 Tab3:** Checklist for the collection of necessary clinical data and follow-up scheme of enrolled patients with EGC

	Baseline information		Follow-up after operation													
	Preoperation	Operation	POD 1	POD 3	POD 7	POD 30	6 months	1 year	18 months	2 years	30 months	3 years	42 months	4 years	54 months	5 years
**Informed consent**	×															
**Demographic information**	×															
**Laboratory tests**	×		×	×	×	×	×	×	×	×	×	×	×	×	×	×
**Chest CT scan**	×							×		×		×		×		×
**Abdominal CT scan**	×						×	×	×	×	×	×	×	×	×	×
**Gastroscopy**	×							×		×		×		×		×
**Abdominal ultrasound**	×						×	×	×	×	×	×	×	×	×	×
**Physical examination**	×						×	×	×	×	×	×	×	×	×	×
**Surgical information**		×														
**Pathology**		×														

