### Quality control

#### Quality control of pathology

The specimen collectors have sampling experience or are guided by an experienced pathologist. The procedures for handling the resected specimens are as follows: First, the pathologist incises the stomach along the greater curvature. Second, the specimen is fully stretched to maintain the original shape, and the stomach is placed on a flat rubber plate with the mucosal side up and pinned at the edge with stainless steel pins. At the edge of the specimen, the entire gastric wall, especially the muscularis, is pulled outward by the needle with a uniform force to extend the mucosa, which is subsequently fixed on the rubber plate to fully expose the lesions of the mucosal surface. Third, the specimen collection is performed within 30 min after the tissue is isolated. Thereafter, we completely immerse the specimen in a volume of 10% neutral buffered formalin 6–8 times that of the specimen for 12–48 h. The tumor lesions are afterwards sectioned along the vertical direction of the tangent line near the cutting edge. Subsequently, the whole gastric wall tissue is cut in parallel at a distance of 4–5 mm, and all tissues are collected for examination. Finally, we dehydrate, embed, and section the tissue for microscopic observation. The detailed procedure is illustrated in Fig. 2.

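### The primary LNM rate takes no stated account of how many nodes were examined, nor, in the retrospective cohort, of whether a D2 was completed, so it may be underestimated

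*Protocol article*

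**What the plan says.** - **Endpoint.** Under Primary endpoint: "The primary endpoint of this study is the rate of LNM". The scope of expanded indications is then explored "based on the presence of LNM by histopathology and the positive rate of LNM with expanded indications for ESD". No node count appears there.
- **Data collected.** Under Data collection, the pathology items include "number of lymph nodes dissected, and total number of LNM", and the surgical items include the degree of dissection. Neither the logistic and ROC plans under Secondary endpoints nor the Statistical analysis section mentions these items.
- **Operation, prospective part.** Study design and setting says that "patients will undergo a D2 gastrectomy in a non-randomized, prospective study". The D2 gastrectomy section lists stations by operation, for example (sentence cut short here): "The scope of LND of D2 distal gastrectomy should include the No. 1, 3, 4sb, 4d, 5, 6, 7, 8a, 9, 11p, and 12a lymph". It lists 11 stations for distal, 10 for proximal and 14 for total gastrectomy, and gives no number of nodes.
- **Operation, retrospective part.** "For the retrospective study, researchers will recruit patients from January 2008 to April 2018, and all enrolled patients must meet the inclusion criteria". The relevant inclusion criterion asks for patients "who can undergo a radical D2 gastrectomy". That describes fitness for the operation, not the operation performed.
- **Pathology quality control.** The handling steps concern the stomach wall and the tumour, for example "The tumor lesions are afterwards sectioned along the vertical direction of the tangent line near the cutting edge". The report template lists LNM but sets no standard for node retrieval.

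**The concern.** LNM status is observed only through the nodes that the surgeon removes and the pathologist finds. In early cancer a patient with LNM may plausibly have only one or two positive nodes, and the chance of finding one then depends on how much of the nodal field was examined. Incomplete examination turns a true positive into an observed negative and cannot do the reverse, so any error of this kind lowers the primary rate.

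The direction matters because the study is meant to support wider use of ESD, and a low LNM rate is the evidence for that. A larger sample would not remove the error. If yield differed between centres, operations or cohorts, observed LNM rates would also differ between them for reasons unrelated to the tumour.

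**Working it through.** **1. The plan's own figure.** Determination of sample size gives a rate of 3%, an allowable error of 1.5 points and a one-sided α of 0.025 (z = 1.960).

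n = z² p(1−p)/d² = 1.960² × 0.03 × 0.97 / 0.015² = 496.8, rounded up to 497. This reproduces. The precision target therefore treats every LNM as detected.

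**2. Observed rate when detection is incomplete.** Let s be the probability that a patient with LNM has at least one positive node found. The article gives no yield data, so s is an assumption.

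- All patients affected: observed = 3.0% × s.
- Only the retrospective patients affected, with the same true rate in both cohorts: observed = 3.0% × (274 + 280 s)/554.

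| s | All affected | Retrospective only |
|---|---|---|
| 0.95 | 2.85% | 2.92% |
| 0.90 | 2.70% | 2.85% |
| 0.80 | 2.40% | 2.70% |
| 0.50 | 1.50% | 2.24% |

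The shortfall runs from 0.15 to 1.5 points in the first case and from about 0.08 to 0.76 in the second. Its upper end, 1.5 points, equals the whole allowable error.

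**3. What yield would give such values of s.** Assume N = 30 nodes in the full field, k of them positive, and n examined at random: s = 1 − C(N−k, n)/C(N, n).

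| n examined | k = 1 | k = 2 |
|---|---|---|
| 10 | 33% | 56% |
| 15 | 50% | 76% |
| 20 | 67% | 90% |
| 25 | 83% | 98% |

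If half of the patients had 15 of 30 nodes examined and the rest all 30:

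- k = 1: 0.03 × (0.5 + 0.5 × 0.50) = 2.25%
- k = 2: 0.03 × (0.5 + 0.5 × 0.76) = 2.6%

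**4. Precision of a restricted analysis at 3%.** Half-width = 1.96 × √(0.03 × 0.97/n).

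- n = 497: ±1.50 points
- n = 447 (10% dropped): ±1.58 points
- n = 249 (half dropped): ±2.1 points

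**5. How far a restriction corrects.** Take the half-and-half scenario with k = 1. Dropping 10% of all patients, all from the low-yield half, moves the observed rate only from 2.25% to 0.03 × (0.5 + 0.4 × 0.5)/0.9 = 2.33%. Dropping the whole low-yield half restores 3.0%, at ±2.1 points. A minimum of 15 nodes would drop nobody and correct nothing. The choice of minimum therefore decides both the correction and the cost.

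**The case against.** **The argument is from silence.** The article nowhere says that a patient counts as negative however few nodes were examined. A reader might infer that from the missing rule, but the full protocol or the analysis plan, neither shown, may contain one. This stands as a limit on the wording. It does not remove the point: the article defines its primary endpoint and describes pathology handling in detail, and in neither place does it connect LNM status to yield.

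**There are safeguards.** Prospective patients undergo D2 with named stations, surgeons need at least 100 gastrectomies, patients not treated per protocol are eliminated, reports follow a common template, and each part of the trial has a standard operating procedure. This stands for the 274 prospective patients and makes the concern weaker there. It does not close the gap, because stations dissected are not nodes retrieved and examined, and surgical experience does not govern the pathologist's search. For the retrospective patients the safeguards reach less far. The D2 section rests on guidelines of 2016 and 2018, whereas these operations date back to 2008, and no section says that a completed D2 is required of them.

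**The bias is not demonstrated.** A reader might conclude that the rate is biased low as a matter of fact. The documents do not support that: field size, yield, number of positive nodes and random retrieval are all assumptions here. The half-and-half scenario moves the rate by 0.75 points (0.4 with two positive nodes), inside the 1.5-point allowable error. This objection stands on size, not on direction.

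**Effect on the logistic model.** A reader might also infer that the model would credit yield differences to tumour features. That requires yield to be correlated with those features, and nothing in the article shows that it is.

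**Conclusion.** The point holds as a possible underestimate of unknown size. As described, LNM is scored from whatever nodes were examined, and the recorded node count and degree of dissection are not used in the endpoint or in any stated analysis. Any resulting error lowers the LNM rate and favours ESD. With assumed detection of 0.95 to 0.50 in all patients, a true 3.0% would be observed as 2.85% to 1.5%; with only the retrospective cohort affected, as 2.92% to 2.24%. The concern is stronger for the 280 retrospective patients (51% of 554), for whom a completed D2 is not required, than for the 274 prospective ones. These figures show what is at stake under assumptions; they do not estimate an actual bias.

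**What to change.** Prespecify the following before LNM is analysed against node count. The timing is put this way because the retrospective pathology reports already exist.

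1. A companion analysis of the primary rate, limited to patients with a completed D2 and at least a stated minimum number of examined nodes. Apply the restriction alike to LNM-positive and LNM-negative patients; dropping only low-yield negatives would push the rate up.
2. A table of LNM by node-count band, cohort and centre.
3. Reporting of both rates whatever their order, with the indication interpreted in light of both.

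The headline rate should not be chosen by its result. Using the restricted rate only when it is higher would take the larger of two nested estimates, which is biased upward even when yield is adequate.

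The cost is wording and one extra table, since node count and degree of dissection are already on the case report form. The restricted interval is wider: at 3%, about ±1.6 points if 10% of 497 are dropped and about ±2.1 points if half are dropped, against ±1.50 in the full set. The sponsor should look at the distribution of node counts, without LNM status, before fixing the minimum. A value set too low removes few patients and corrects little.
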